## Abstract

**Background:**

A strong evidence base exists regarding routine and emergency services that can effectively prevent or reduce maternal and new-born mortality. However, even when skilled providers care for women in labour, many of the recommended services are not provided, despite being available. Barriers to the provision of appropriate childbirth services may include lack of availability of supplies, limited health worker knowledge and confidence, or inadequate time. The WHO Safe Childbirth Checklist (SCC) includes reminders for evidenced-based practices at specific points in the childbirth process. Zambia is currently considering nation-wide adoption of the SCC, but there is a need for context-specific evidence. Beginning in September 2017, a program is being implemented in Nchelenge District to pilot use of the SCC, along with coaching that focuses on strengthening the systems that allow the essential practices in childbirth to be performed.

**Methods:**

This study will use a pre-post study design to measure health worker adherence to the essential practices for delivery care outlined in the SCC. Data will be collected through observations of health workers as they care for mothers during childbirth at four facilities. Data collection will take place before the start of the intervention, at 3 months, and at 6 months post-intervention. The primary outcome interest is the change in the average proportion of essential childbirth practices completed. A health worker questionnaire will be administered at the time that the SCC is introduced and 6 months later to gather their perspectives on incorporating the SCC into clinical practice in Zambia.

**Discussion:**

Findings are expected to inform plans for introducing the SCC in Zambia. This evaluation will aim to understand uptake and impact of the SCC and associated coaching in the context of a basic level of mentorship that the government could feasibly provide at a national scale.

**Trial registration:**

Clinical Trials.gov (NCT03263182) Registered August 28, 2017.

## Background

Despite some recent improvements, Zambia continues to experience high maternal and neonatal mortality rates. As of 2014, the maternal mortality ratio was estimated to be 398 per 100,000 live births [1], far above the average in developing countries of 239 deaths per 100,000 [2], while the neonatal mortality rate for 2009 to 2013 was 24 deaths per 1000 live births [1].

Maternal and new-born mortality can be prevented through the provision of basic health services for all women and appropriate emergency obstetric and new-born care (EmONC) services for women and infants who need it [3]. Although evidence suggests that basic services during pregnancy, at the time of delivery, and post-delivery, can prevent maternal and new born deaths, there are a number of barriers that prevent provision of basic maternity services. For instance, a critical challenge in Zambia and many other countries is that not all women deliver at a health facility and therefore do not have access to skilled health workers at the time of delivery [1]. A further challenge is that even when mothers go to health facilities, the appropriate staffing and supplies may not always be available to support the provision of essential childbirth services. Specifically, the facility must be staffed by a skilled birth attendant (SBA), which is an accredited health professional such as a midwife, clinical officer, doctor, or other health worker who has been educated and trained to proficiency in the skills needed to manage normal (uncomplicated) pregnancies, childbirth and the immediate postnatal period, and in identification, management and referral of complications in women and new-borns [4]. An SBA not only needs specific training to be able to provide the EmONC signal functions, but they should also have access to equipment, drugs, supplies, a referral system, and functioning communication and transportation infrastructure. Zambia’s health worker shortages are most acute in rural and remote areas with an estimated 12.4 clinicians per 10,000 persons as compared to 18.7 per 10,000 persons living in urban areas [5]. Both these ratios fall below the World Health Organization’s recommended threshold of 22.8 clinicians per 10,000 [6]. Even when mothers attend facilities for deliveries and the appropriate staffing and supplies are available, there remains a final barrier in assuring that the appropriate services are actually provided in a high-quality and comprehensive way. Possible factors associated with poor quality services could be limited health worker knowledge, confidence, and time.

The Safe Childbirth Checklist (SCC), developed by the World Health Organisation (WHO), is one tool that may help to improve the quality and safety of delivery services. The WHO SCC is based on the experience of the Safe Surgical Checklist, which demonstrated significant reductions in surgical complications and deaths [7]. The SCC consists of reminders to prompt evidenced-based practices that are essential to providing quality care at the time of labour and delivery. The tool is designed for use by birth attendants at four critical “pause points” in the delivery process: (1) at admission, (2) just prior to delivery, (3) in the immediate post-partum period, and (4) prior to discharge. A number of published studies have examined the process and effectiveness of introducing the SCC in specific country contexts, including India [8–13], Sri Lanka [14], Italy [15], Iran [16], and Namibia [17, 18]. A pilot study in India found that the delivery of evidence-based essential birth practices at each birth event increased from an average of 10 out of 29 practices prior to introduction of the SCC to an average of 25 out of 29 practices after the SCC had been introduced. However, there was no overall effect on mortality [19].

While the SCC has been implemented in sub-Saharan countries including Namibia and Uganda, the SCC has not previously been implemented in Zambia where maternal mortality is higher [20, 21]. The Ministry of Health (MOH) is currently considering nation-wide adoption of the SCC, but there is a need for context-specific evidence, specifically evidence about how to successfully implement the SCC, to generate lessons about the roll-out process in Zambia. This study will be unique compared to many previous studies that have investigated SCC adoption because the adoption of the tool will be integrated into a scalable, national framework for mentorship to health facilities.

## Objectives

Can the introduction of the Safe Childbirth Checklist and associated mentorship improve the adherence of skilled birth personnel to the essential practices of childbirth delivery?

The key outcome to be measured is the average proportion of essential childbirth practices completed.

## Methods

### Trial design

This is a pre-post study design that will include observing consecutive deliveries carried out in four selected health facilities before and after the introduction of the SCC. The study protocol was registered in the Clinical Trials.gov, a resource provided by the U.S. National Library of Medicine (NCT03263182).

### Study setting

The WHO SCC will be introduced in eight purposively selected health facilities in Nchelenge District, Luapula Province. Nchelenge District was chosen by the MOH to be the location for this pilot based on need. The eight facilities were selected based on criteria including: high demand for services, perceived need for support for quality improvement, and presence of a SBA to mentor. However, data collection for this evaluation will take place in only four facilities with high volumes for the observations to occur. The four sites include three health centers and one general hospital.

### Eligibility criteria

For facility observations, all consecutive deliveries will be observed. If a pregnant woman or health worker declines to participate in the consent process, no observations will be recorded.

### Interventions

The SCC will be piloted as part of a broader program to improve delivery of routine care for all women through a systems improvement approach focusing on health worker knowledge and skills; availability of supplies and equipment; ensuring good documentation and data use; and creating an enabling environment at health facilities in Zambia. This broader program is taking place in 14 districts in Zambia and aims to increase the availability, accessibility, and quality of maternal and newborn health services. While this program will be operating in 14 districts (and is being evaluated separately), the introduction of the SCC as a part of this package will be piloted in one district. The SCC intervention will involve several key steps and components:Adaptation of the WHO designed SCC tool to Zambia to produce a tool that is fully relevant to the Zambian context.Development of coaching tools to capture performance and track progress at individual and facility level.Training of coaches and district team to the adapted WHO SCC and coaching tools.Facility launches of the WHO SCC at all the eight target facilities to ensure facility staff understand the intervention.Coaching and supporting facility-level health workers on using the SCC by directly observing SBAs conduct deliveries as well as review of records for deliveries happening in the absence of the coach.Based on the data generated from the coaching tools, generate dashboards to be reviewed with coaches, facility staff and district teams so as determine challenges and identify issues of escalation within the health care system

### Outcomes

The primary outcome variable of interest is the change in the average proportion of essential childbirth practices completed per birth out of those observed from the list of selected tasks. We have developed a list of selected tasks that represent a sub-set of items in the SCC which are tasks that can be visually observed and that are non-conditional (in other words they should be performed on all mother-infant pairs regardless of health status). The list of selected tasks includes the following 21 items:Was vaginal exam performed to check dilation?Were sterile gloves used for the vaginal exam?Was partograph started?Did the health worker review danger signs with the mother (and companion)?Were water and soap used to clean hands alcohol rub used on the mother just before delivery?Were sterile gloves used at the time of delivery?Were all of the following supplies available at the bedside? (Clean scissors or blade, Clean cord tie or clamp, Aspiration bulb or mucus extractor, Neonatal bag and mask, Oxytocin 10 units in syringe)Did the primary health worker managing the delivery communicate with a health worker assistant to say that the birth will happen shortly and ask for assistance?Was oxytocin administered?Was newborn weight taken?Was newborn temperature taken within 1 h after birth?Was baby placed skin-to-skin on mother’s abdomen?Was breastfeeding initiated?Was maternal temperature obtained at admission?Was maternal blood pressure obtained at admission?Was maternal blood pressure obtained at discharge?Was maternal temperature obtained at discharge?Was newborn temperature taken at discharge?Did health worker confirm that infant is feeding well?Did health worker discuss family planning options with mother?Did health worker plan a follow-up visit for mother and newborn and discuss danger signs?

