### Statistical methods

For the primary outcome, data from each delivery will be considered as a percentage of the 21 SCC items that were practiced, or in other words each pause point observation will be assigned a score from 0 to 100%. The differences over time will be examined using linear regression and accounting for clustering at the facility level as well as transformation to account for the bounded data. We will also consider clustering at the level of the primary provider responsible for overseeing the delivery. Sub-analysis will be conducted to account for the impact of availability of supplies on conduct of tasks. Within each facility in the sample, we will also compare the average score for all deliveries at baseline, midline and end line using a paired, weighted t-test to account for differences in the standard errors. Finally, to better explore meaningful change due to the program, we will examine if there is an increase in the proportion of births where the majority (75%) of tasks are completed; specifically, we will examine if the difference overtime in the average proportion of births where 75% of tasks were completed increases due to the intervention. To this end we will run individual-level logistic regression, accounting for clustering at the facility level.

For the health worker questionnaires, we will report descriptive statistics only, with baseline and end line comparisons.

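### The 21-item score includes tasks that cannot apply to every delivery, and the article gives two different denominators for it

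*Protocol article*

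**What the plan says.** All references are to the protocol article.

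- **Items.** Outcomes describes the 21 tasks as "non-conditional (in other words they should be performed on all mother-infant pairs regardless of health status". The list includes "Were sterile gloves used for the vaginal exam", directly after an item asking whether that exam was done. It also includes newborn temperature within an hour, skin-to-skin placement, breastfeeding, newborn temperature at discharge, infant feeding, and maternal blood pressure and temperature at discharge.
- **Births.** Eligibility criteria states: "For facility observations, all consecutive deliveries will be observed". The only exclusion is refusal by the woman or the health worker. Under Study setting, "The four sites include three health centers and one general hospital".
- **Denominator.** Outcomes defines the primary variable through practices "completed per birth out of those observed from the list of selected tasks". Statistical methods scores each delivery as the share of all 21 items that were practised. It also plans a logistic regression on whether 75% of tasks were completed.
- **Supplies.** One of the 21 items is "Were all of the following supplies available at the bedside". Statistical methods adds: "Sub-analysis will be conducted to account for the impact of availability of supplies on conduct of tasks".

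**The concern.** The label says that every item applies to every mother and infant, but the list and the eligibility rule do not bear this out. The glove item has no meaning if no exam took place. Five items need a living newborn. The discharge items need mother and baby to be discharged from the facility and not referred elsewhere. Nothing under Eligibility criteria limits the sample to live births or to pairs discharged from the site.

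This would do no harm if the score left such items out. One section suggests that it does, and the other divides by 21 throughout. Under the second rule a birth can score low because of what happened to the mother or baby, not because of what the health worker did. With few births per facility and round, a chance difference in case mix could then pass for a change in practice.

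The supplies question is separate. If supply availability is used to explain the overall score, one component of that score is supply availability itself.

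**Working it through.** **The plan's own figure.** From Sample size: z-values 1.96 and 0.84, s = 17% at both times, intra-class correlation 0.25, n = 6.5 births per site, difference 24 points.

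c = 1 + (1.96 + 0.84)² × [(0.17² + 0.17²) × (1 + 5.5 × 0.25)] / (6.5 × 0.24²) = 1 + 1.0762 / 0.3744 = 3.87, which rounds up to the four facilities. Solved for the difference at c = 4, the formula gives 23.5 points. The stated 24 reproduces and is not in dispute. It serves below as the scale of the planned effect.

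**Inapplicable items per birth (k).**

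- No vaginal exam: k = 1 (gloves). Under a fixed 21 the omission costs 2/21 = 9.5 points instead of 1/21 = 4.8.
- Stillbirth or early death: k = 5 (two newborn temperatures, skin-to-skin, breastfeeding, feeding). Counting newborn weight, which is arguable, k = 6.
- Referral out before discharge: k = 3 for the items that name discharge. If the last three items on the list also belong to that stage, which the article does not label, k = 6.

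**Highest attainable score under a fixed 21: (21 − k)/21.**

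| k | Cap |
|---|---|
| 1 | 20/21 = 95.2% |
| 3 | 18/21 = 85.7% |
| 5 | 16/21 = 76.2% |
| 6 | 15/21 = 71.4% |

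**The 75% endpoint.** 0.75 × 21 = 15.75, so 16 items are needed. With k = 5, all 16 remaining items must be done; one miss gives 15/21 = 71.4%, a failure. Over applicable items the same birth would need 0.75 × 16 = 12. With k ≥ 6 the endpoint cannot be met even with every applicable item done. Each birth misclassified in this way moves the round's proportion by 1/28 = 3.6 points.

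**The mean.** Data collection methods sets at least seven births per facility, so 4 × 7 = 28 per round. At 58% adherence on applicable items and k = 5, an affected birth loses 0.58 × 5/21 = 13.8 points. This moves:

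- the round mean by 13.8/28 = 0.5 points;
- a single facility's mean by 13.8/7 = 2.0 points.

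The share of affected births is not in the article. Assuming 2% to 20% with k = 5:

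- mean at 58% adherence: 13.8 × 0.02 to 13.8 × 0.20 = 0.3 to 2.8 points lower;
- mean at 34% adherence: 0.34 × 5/21 = 8.1 points per affected birth, so 0.2 to 1.6 points lower;
- change over time, if the share is equal in both rounds: 24 × 5/21 = 5.7, so 0.1 to 1.1 points smaller.

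**Supplies.** The item carries 1/21 = 4.8 points. If the outcome is the 21-item score, births with and without full bedside supplies differ by that much by construction, whatever else is done.

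**The case against.** A reader might infer that inapplicable items are scored as failures. The article does not establish this. The Outcomes wording can be read as dropping items that could not be observed, which is close to the remedy proposed here. What stands is that this wording and the fixed 21 in Statistical methods differ. The Outcomes wording is not clear in itself either, because Sample size uses the word observed for items that were performed.

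The glove item is the weakest example. The definition of non-conditional is normative and concerns health status: if every woman should be examined, every woman should have a gloved exam. Counting both steps is then a defensible choice, though it should be made deliberately.

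The phrase mother-infant pairs may imply a live newborn, but Eligibility criteria does not say so. The article gives no stillbirth or referral rate. Its nearest figure, in Background, is 24 neonatal deaths per 1000 live births, which covers the whole neonatal period. A large bias in the primary mean is therefore not supported.

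It is also tempting to call the supplies sub-analysis circular outright. The article does not name its outcome, and an analysis task by task would fit the wording. The overlap arises only if the overall score is used. Setting the 4.8 points against the planned 24 would also mix two contrasts: supplies present versus absent, and change over time.

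Finally, the data sheets are not shown and may already have a code for not applicable. Its absence cannot be claimed.

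**Conclusion.** The point holds in a limited form. The article states two denominators for its primary outcome. It calls non-conditional a list in which at least five items cannot apply after a stillbirth or early death, and others cannot apply after referral out, while the eligibility rule admits such births.

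The consequence depends on which denominator is used. If it is the fixed 21, the loss in the round mean is about 0.5 points per affected birth, small beside 24. That rests on five inapplicable items, 58% adherence and 28 births; only the share of affected births, which is unknown, would make it matter. The within-facility comparisons are more sensitive, at about 2 points per affected birth among seven. The main exposure is the 75% endpoint, where five inapplicable items leave no room for a single miss and six rule out success.

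The supplies overlap is conditional on the overall score being the outcome of that sub-analysis. It is worth correcting because the correction is trivial.

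**What to change.** 1. In Statistical methods, replace the fixed 21 with the rule that Outcomes points to: each birth is scored over the items that were both applicable and observed.
2. Record not applicable and not observed as categories separate from not done, and state which items become not applicable when: gloves if no exam was done, the newborn items if there is no living newborn at that stage, the discharge items if mother or baby was referred out. If the data sheets already do this, say so.
3. Apply the 75% threshold to the same denominator.
4. Qualify the non-conditional label accordingly.
5. If the supplies sub-analysis uses the overall score, use a 20-item score there without the bedside supplies item, and keep that item as the explanatory variable only.

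The cost is a few lines of scoring rules and, at most, one extra code on the form. No more births are needed and care does not change. The downside is that denominators vary slightly between births. Reporting the number of items not applicable and not observed, by round and facility, would let readers see whether that variation matters.

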### Study timeline

**Table Taba:** 

	**M1**	**M2**	**M3**	**M4**	**M5**	**M6**	**M7**	**M8**	**M9**	**M10**	
**Hire and train data collectors**	X										
**Baseline data collection**	X										
**Launch of intervention**			X	X							
**Midline data collection**							X	X			
**End line data collection**										X	
**Data analysis**											X

### Sample size

We calculated the expected power that this observation period will give us to detect changes in practices based on data about delivery volumes at the four sites, using the following formula [22]:

$$ c=1+{\left({z}_{\alpha /2}+{z}_{\beta}\right)}^2\ast \frac{\left[\left({s}_0^2+{s}_1^2\right)\ast \left(1+\left(n-1\right)\rho \right)\right]}{n{\left({m}_0-{m}_1\right)}^2} $$

Due to the small number of facilities the equation utilizes the difference in the main proportion assuming a t-test will be utilized [23]. Where: c = number of facilities needed, Z_a/2_ and Z_B_ = type I (1.96) and type II error (0.84) respectively, s_0_ and s_1_ are the standard error at baseline (17%), ρ = interclass correlation (0.25). We estimate that at baseline 34% (m_0_) of the 15 SCC items will be observed per birth, based on previous work in India indicating that an average of 9.8 out of 29 items were observed per birth at baseline [12]. According to the Health Management Information System data from January to October 2016, there was an average of 390 deliveries per month across the four study facilities. This means that if we observed all deliveries for approximately 48 h in each site, we could expect to observe an average of 6.5 (n) deliveries per site. With such a sample size, the calculations indicate that we could detect an absolute increase of 24% in the proportion of adherence to SCC essential best practices (m_1_ = 58%).

For the secondary outcomes related to health workers characteristics and feedback, all health workers in the four study sites will be invited to participate as a convenient sample.

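### The 24-point detectable increase comes from a formula for two independent sets of facilities, but the same four facilities are observed before and after

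*Protocol article*

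**What the plan says.** The Trial design section describes a single group of sites studied by "observing consecutive deliveries carried out in four selected health facilities before and after the introduction of the SCC". Data collection methods has observations in three rounds: baseline, midline and end line. No separate comparison facilities are described.

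The Sample size section opens with "We calculated the expected power that this observation period will give us to detect changes in practices based on data about delivery volumes". It gives a formula for c, the number of facilities needed, and says that a t-test is assumed because facilities are few. The inputs are normal quantiles for "type I (1.96) and type II error (0.84) respectively", a spread of 17% in each round, an "interclass correlation (0.25"), a baseline mean of 34% and an observation window of about 48 hours, from which "we could expect to observe an average of 6.5 (n) deliveries per site". The result is a detectable rise from 34% to 58%, put as "we could detect an absolute increase of 24% in the proportion of adherence to SCC essential best practices".

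Statistical methods plans a linear regression over time that accounts for clustering by facility, with provider clustering also considered. It adds a comparison of rounds within each facility by a paired, weighted t-test.

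**The concern.** The formula adds the variances of the two rounds, inflates both by the full design effect 1 + (n − 1)ρ, and has no term for the correlation of a facility with itself over time. That is the variance of a difference between two independent groups of c facilities each. Here one group of four supplies both rounds.

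The mismatch has two consequences, which pull in opposite directions:

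- A facility that is better or worse than the others in both rounds contributes nothing to the change. Precision improves.
- Four facilities give four changes, so a paired comparison has 3 degrees of freedom. Two groups of four would have 6. Precision worsens.

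Neither effect is in the calculation. The 24 points is the article's only statement of what the study can detect, and the Discussion foresees a particular response if only limited changes are seen. A reader judging whether a small observed change was within the study's reach has no other figure to use.

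**Working it through.** **Inputs, all from Sample size.** z-values 1.96 and 0.84, sum 2.80, squared 7.84; s0 = s1 = 0.17 (labelled a standard error, but used in the formula as a standard deviation between deliveries, and so treated here); ρ = 0.25; n = 6.5, from 390 / 4 = 97.5 births per site per month, over 2 of 30 days; difference 0.24; four facilities. The one input not given is r, the correlation of a facility's underlying level between rounds. It is an assumption here and is varied from 0 to 1.

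**Step 1: the plan's figure.** s0² + s1² = 2 × 0.0289 = 0.0578. Design effect = 1 + 5.5 × 0.25 = 2.375.

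c = 1 + 7.84 × 0.0578 × 2.375 / (6.5 × 0.24²) = 3.87, rounded up to 4.

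Solved for c = 4, the difference is √[7.84 × 0.0578 × 2.375 / (6.5 × 3)] = 0.235. The stated 24 points reproduces. A t-test of two independent groups of four facilities (6 df) gives 24.5 points, so the +1 in the formula is an adequate small-number correction for that design.

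**Step 2: the variance when facilities repeat.** For the mean of four facility changes,

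Var = 2s²[(1 − ρ)/n + ρ(1 − r)] / 4.

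At r = 0 the bracket is 0.75/6.5 + 0.25 = 0.365, which equals 2.375/6.5. The plan's variance is thus the special case in which a facility's level in one round says nothing about its level in the next.

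**Step 3: detectable change, two rounds, paired t on 3 df.** For 80% power at two-sided 5%, the change must be 4.256 standard errors (noncentral t, 3 df).

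| r | SE of mean change | Detectable at 80% power | Power at 24 points |
|---|---|---|---|
| 1 | 0.0408 | 17.4 points | 96% |
| 0.8 | 0.0489 | 20.8 points | 89% |
| 0.5 | 0.0589 | 25.1 points | 77% |
| 0 | 0.0727 | 30.9 points | 61% |

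The detectable change equals 24 points at r of about 0.58.

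**Step 4: the number of births.** Data collection methods does not use 48 hours. It sets a minimum of 3 days, or as long as it takes to see seven births. At the stated volumes 3 days gives 97.5 × 3/30 = 9.75 births per site on average. On the same 3-df test:

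| r | n = 7 | n = 9.75 |
|---|---|---|
| 1 | 16.7 points | 14.2 points |
| 0.8 | 20.3 points | 18.2 points |
| 0.5 | 24.6 points | 23.0 points |
| 0 | 30.6 points | 29.3 points |

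**Step 5: the degrees of freedom.** A facility-by-round model using all three rounds would have (4 − 1)(3 − 1) = 6 residual df. The multiplier is then 3.367, and with n = 6.5 the detectable change is 13.7 points at r = 1 and 24.5 points at r = 0.

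**The case against.** The best defence is that the number itself has not been shown to be wrong. The arithmetic is right, and 24 lies inside the 21 to 25 points obtained for r between 0.8 and 0.5. The extremes of 17 and 31 need r = 1 or r = 0, and the article gives no information on r. All of this stands, and it limits the point to the choice of formula.

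A second defence is that 3 df is only one reading. The primary analysis is a delivery-level regression with facility clustering, and a three-round facility model has 6 df, under which 24 points is about right or conservative at every r. This also stands in part. However, the sample size section itself assumes a t-test because facilities are few, and a baseline versus end line comparison of four facilities has 3 df. On either reading the formula used does not describe the design.

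A third is that the planned 3 days would yield more births than 6.5. With 9.75 births, 24 points is reached on 3 df for any r above about 0.43. That is a reason to recompute with the right n, and it does not rescue the formula.

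A reader might go further and infer that the study is underpowered, or the opposite, that ignoring the pairing is safely conservative. The article supports neither. With n = 6.5 and 3 df, 24 points is optimistic below r of about 0.58 and conservative above it. Nor does the article tie its remark about limited changes to 24 points, or use the figure as a success threshold.

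**Conclusion.** The point holds as a mismatch between formula and design. The stated 24 points is correctly calculated for two independent sets of four facilities, and the study has one set observed repeatedly. With the plan's inputs and a two-round paired t on 3 df, the detectable change at 80% power is 17 to 31 points over r = 1 to 0, and 21 to 25 points over r = 0.8 to 0.5. Power at 24 points runs from 96% down to 61%. The direction of any error is undetermined.

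These figures assume equal spread in both rounds, the 17% taken as a standard deviation, an equal number of births at each site, and a value of r that the article does not state. Severity is moderate: the figure describes what a fixed observation period can detect and does not set the number of sites.

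**What to change.** In Sample size, replace the formula with the repeated-facility variance 2s²[(1 − ρ)/n + ρ(1 − r)]/4. Use degrees of freedom that match the planned facility-level analysis: 3 for baseline versus end line in four facilities. Reconcile n with the observation rule in Data collection methods: on 3 df, n = 7 gives about 17 to 31 points and n = 9.75 about 14 to 29 points over the full range of r. State the values of r considered and why, and report the detectable change as a range over them instead of the single figure of 24.

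The cost is one rewritten paragraph, with no extra births or sites. The stated detectable change may become less favourable.
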